## Abstract

Early-onset neonatal sepsis (EONS), a bacterial infection that occurs within 72 h after birth, is associated with high likelihood of neonatal mortality. Latamoxef, a semi-synthetic oxacephem antibiotic developed in 1980s, has been brought back into empirical EONS treatment in recent years. In the preliminary work, we established a population pharmacokinetics (PPK) model for latamoxef in Chinese neonates. Moreover, in order to better guide clinical treatment, we conducted dose simulation and found that ascending administration frequency could improve the target rate of 70% of patients having a free antimicrobial drug concentration exceeding the MIC during 70% of the dosing interval (70% fT > MIC). Accordingly, this study is aimed to compare the 70% fT > MIC, efficacy and safety between conventional regimen and PPK model regimen for rational use of latamoxef in EONS treatment. A single-blind, multicenter randomized controlled trial (RCT) for latamoxef will be conducted in Chinese EONS patients. Neonates (≤3 days of age, expected number = 114) admitted to the hospital with the diagnosis of EONS and fulfilling inclusion and exclusion criteria will be randomized (ratio of 1:1) to either a conventional regimen (30 mg/kg q12h) or model regimen (20 mg/kg q8h) latamoxef treatment group for at least 3 days. Primary outcome measure will be 70% fT > MIC and secondary outcome indicators will be the latamoxef treatment failure, duration of antibiotic therapy, changes of white blood cell count (WBC), C-reactive protein (CRP) and procalcitonin (PCT), blood culture results during administration and incidence of adverse event (AE)s. Assessments will be made at baseline, initial stage of latamoxef treatment (18–72 h) and before the end of latamoxef treatment. Ethical approval of our clinical trial has been granted by the ethics committee of the Beijing Children’s Hospital (ID: 2020-13-1). Written informed consent will be obtained from the parents of the participants. This trial is registered in the Chinese Clinical Trial Registry (ChiCTR 2000040064).It is hoped that our study will provide a clinical basis for the rational clinical use of latamoxef in EONS treatment.

## Introduction

Neonatal sepsis, a leading cause of mortality in neonates worldwide, is divided into early-onset (EONS) and late-onset neonatal sepsis (LONS) (Polin, 2012; Shane et al., 2017). EONS occurs within 72 h after birth and the mortality rate of EONS was reported as high as 30% in high-income countries and up to 60% in low-income countries (Thaver and Zaidi, 2009; Stoll et al., 2011). Accordingly, rational anti-infective treatment of EONS plays a crucial role in preventing neonatal mortality and protecting the health of neonates. However, antibiotic resistance, off-label use and adverse reactions plague EONS treatment. Because the prevalence of antibiotic-resistant bacterial strains has increased dramatically, recently there has been a renewed interest in historical antibiotics for EONS treatment (Thaver and Zaidi, 2009; Stoll et al., 2011), such as latamoxef. Latamoxef, a second-generation semi-synthetic oxacephem antibiotic, developed in 1980s, is mainly used to treat infections, caused by Gram-positive and -negative aerobic, as well as anaerobic bacteria (Carmine et al., 1983). Although latamoxef has been used for the anti-infective treatment of neonates since 1980s, limited neonatal pharmacokinetics (PK) data and off-label use remain a vexing problem for this drug being used in the field of EONS treatment.

To assess the PK features of latamoxef in neonates, we performed a population pharmacokinetics (PPK) study of latamoxef in Chinese neonates and established a PPK model for them (Carmine et al., 1983). Current body weight, birth weight, and postnatal age have been identified as significant covariates influencing latamoxef clearance (Qi et al., 2019). Moreover, to develop a rational dosing regimen for latamoxef, we conducted dose simulation and found that ascending administration frequency could improve the target rate of 70% of patients having a free antimicrobial drug concentration exceeding the MIC during 70% of the dosing interval (70% fT > MIC) (Qi et al., 2019). Based these findings, to provide more pharmacodynamics (PD) data for generalizing this PPK model-based regimen, we plan to conduct a single-blind, multicenter randomized controlled trial (RCT) and compare the 70%fT > MIC, efficacy and safety between conventional regimen and PPK model regimen for latamoxef in EONS treatment for the first time.

## Methods and Design

### Trial Design

The proposed clinical trial will be a randomized, single-blind and multicenter intervention study for latamoxef in EONS treatment. This trial is registered in the Chinese Clinical Trial Registry (ChiCTR 2000040064) and is in full adherence to the principles of the Declaration of Helsinki and Good Clinical Practice (GCP) guidelines. This trial will be conducted at three hospitals in China (Table 1), and 114 EONS patients will be randomly enrolled to two regimen groups with a ratio of 1:1 from November 2020 to December 2021. The schematic diagram of study design is shown in Figure 1.

**TABLE 1 T1:** Hospitals participating in this RCT.

Code	Participating hospitals
1	Beijing friendship hospital
2	Beijing obstetrics and gynecology hospital
3	Children’s hospital, Capital institute of pediatrics

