### Sample Size Estimates

According to our preliminary PPK study and dose simulation for latamoxef in neonates (Qi et al., 2019), 60.2% of neonates using conventional treatment regimen (30 mg/kg q12 h) reached 70% fT > MIC and 80.1% of neonates using model treatment regimen (20 mg/kg q8h) reached 70% fT > MIC with MIC of 2 mg/L, respectively. We conducted sample size estimation for superiority design by using PASS 15.0 (NCSS, Kaysville, Utah, United States). To achieve a statistical power of 80% (one-sided type 1 error of 5%), the calculated sample size of each treatment group was 57 patients per treatment group (114 in total) with the ratio of 1:1. Taking into account a 10% dropout rate, 64 patients per treatment group (128 in total) will be required.

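### The enrolment target is given as both 114 and 128: the Abstract and Trial Design omit the 10% dropout allowance that Sample Size Estimates requires, which costs about 4 points of power

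*Protocol article*

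**What the plan says.** Three places in the protocol article bear on the number of infants.

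- Trial Design: "114 EONS patients will be randomly enrolled to two regimen groups with a ratio of 1:1", at three hospitals, from November 2020 to December 2021.
- Abstract: "expected number = 114", attached to the neonates who are to be randomised.
- Sample Size Estimates: "the calculated sample size of each treatment group was 57 patients per treatment group (114 in total) with the ratio of 1:1", followed by "Taking into account a 10% dropout rate, 64 patients per treatment group (128 in total) will be required".

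The last section also gives the design inputs: superiority, 80% power, a one-sided 5% type 1 error, and target-attainment rates of 60.2% and 80.1% from the group's earlier simulation.

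**The concern.** Sample Size Estimates keeps two quantities apart: 114 is the calculated size, and 128 is what must be enrolled so that about 114 remain after dropout. Trial Design and the Abstract use the first of these as the number randomised. No part of the article reconciles them.

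This total decides when enrolment stops. Three sites and an external randomisation vendor need a single figure. A site working from Trial Design would stop 128 − 114 = 14 infants short of the stated requirement. A later reader could not tell whether stopping at 114 was planned or a shortfall, or whether continuing to 128 was planned or an overrun.

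The allowance matters for the primary outcome. It is computed from plasma concentrations obtained by opportunistic sampling at 18–72 h, so an infant without a usable sample has no measured concentration to enter the calculation.

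**Working it through.** **Inputs** (Sample Size Estimates): p1 = 0.602 ("60.2% of neonates using conventional treatment regimen (30 mg/kg q12 h) reached 70% fT > MIC"); p2 = 0.801 ("80.1% of neonates using model treatment regimen (20 mg/kg q8h) reached 70% fT > MIC with MIC of 2 mg/L"); one-sided α = 0.05 (z = 1.645); power 80% (z = 0.842); dropout 10%; difference 0.801 − 0.602 = 0.199.

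**1. The dropout step reproduces.** 57 / 0.9 = 63.3, rounded up to 64 per group; 2 × 64 = 128. So 128 is 114 with the allowance added, and 114 is the number meant to remain.

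**2. The 57 per group does not reproduce.** The mean rate is 0.7015, so √(2 × 0.7015 × 0.2985) = 0.647. Also p1(1 − p1) + p2(1 − p2) = 0.2396 + 0.1594 = 0.3990, with square root 0.632.

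- Pooled: n = [1.645 × 0.647 + 0.842 × 0.632]² / 0.199² = 1.596² / 0.0396 = 64.3, so 65 per group.
- Unpooled: n = (1.645 + 0.842)² × 0.3990 / 0.0396 = 62.3, so 63 per group.
- Arcsine: 64 per group. The log-odds (68) and continuity-corrected (75) versions lie further away.

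None of these gives 57.

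**3. Power at the sample sizes in play**, one-sided 5%. Pooled: Φ[(0.199√n − 1.645 × 0.647) / 0.632]. Unpooled: Φ[0.199√n / 0.632 − 1.645]. The last column enumerates the two binomials exactly for the uncorrected chi-square (z) test.

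| Situation | Evaluable per group | Pooled | Unpooled | Exact |
|---|---|---|---|---|
| 114 randomised, 10% lost (57 × 0.9 = 51.3) | 51 | 71.4% | 72.7% | 72.5% |
| 114 randomised, none lost; or 128 randomised, 10% lost (64 × 0.9 = 57.6) | 57 | 75.6% | 76.8% | 75.7% |
| 128 randomised, none lost | 64 | 79.8% | 80.9% | 80.4% |

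**4. Splitting the shortfall from 80%.**

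- Missing allowance (57 down to 51 per group): 75.6 − 71.4 = 4.2 points pooled, 76.8 − 72.7 = 4.1 unpooled, 75.7 − 72.5 = 3.2 exact.
- Base calculation (80% down to the power at 57): 80 − 75.6 = 4.4 points pooled, 80 − 76.8 = 3.2 unpooled, 80 − 75.7 = 4.3 exact.
- Cross-check: if 57 per group is accepted as giving 80%, 51 per group gives Φ[(1.645 + 0.842) × √(51/57) − 1.645] = 76.0%, again a loss of 4 points.

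**5. Enrolment that would deliver 80% after 10% loss on the stated inputs.** 63 / 0.9 = 70 and 65 / 0.9 = 72.2, rounded up to 73 per group: about 140 to 146 in total.

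**The case against.** The fairest defence is that 114 means evaluable infants. The Abstract calls it an expected number, which could simply echo the calculated size, and Sample Size Estimates shows that the allowance was planned. On this view two sentences were not updated. That weakens the Abstract as evidence, but Trial Design applies 114 to infants being enrolled at random and does not say that they are evaluable or completers. Nor does condensation into an article explain it: two statements conflict, rather than a detail being left out.

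It is also fair to say that 51 per group is conditional. The article does not define dropout as loss of the primary outcome, the infants are inpatients sampled within 72 h, and the analysis section invokes intention-to-treat for missing data. Actual losses could be below 10%. This stands, and the power at 51 per group should be read as what follows if the whole assumed 10% is unevaluable. Intention-to-treat does not, however, supply a concentration that was never measured.

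A reader might infer three stronger things, none of which the document supports:

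- *That leaving out the allowance takes power from 80% to about 71%.* It does not. On the stated inputs 57 per group already gives only about 76–77%, so roughly half of the fall belongs to the base calculation.
- *That writing 128 everywhere restores 80%.* It restores consistency only. After 10% loss, 128 leaves about 57 per group.
- *That power should be quoted for a two-sided test here.* Sample Size Estimates specifies a one-sided 5% error, while the analysis section gives a p-value threshold without saying whether it is one- or two-sided. That is a separate question, and the enrolment mismatch should not be charged with its consequences.

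**Conclusion.** The contradiction stands as written and concerns a core design figure. The 114 in Trial Design, echoed in the Abstract, omits the allowance that Sample Size Estimates says is needed. Its own effect is moderate: about 4 points of power, from about 76–77% at 57 evaluable per group to about 71–73% at 51. This assumes the stated rates, a one-sided 5% test, and loss of the full 10% from the primary outcome.

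The remaining 3 to 4 points below 80% arise because the stated inputs call for 63–65 evaluable per group rather than 57. The two problems should be corrected together, since settling the total without rechecking the 57 would fix a number that does not deliver the stated power.

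**What to change.** Recheck the base calculation of 57 per group first. Then state one randomised total, in the same words, in the Abstract, Trial Design and Sample Size Estimates, label any evaluable number as such, and give the randomisation vendor the same total. Beside it, report the power delivered after dropout:

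- **114 randomised:** about 51 evaluable per group and about 71–73% power. This is a change of wording only.
- **128 randomised:** about 57 evaluable per group and about 76–77% power. This is the protocol's own stated requirement, but it means 14 more infants than Trial Design plans, from the same three hospitals and recruitment window, so it is not merely an edit.

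If the recheck confirms 63–65 per group and the sponsor wishes to keep 80% power with 10% dropout, the total would be about 140 to 146, which is 26 to 32 more than Trial Design plans. Otherwise the stated 80% should be replaced by the power that the chosen total provides.

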**FIGURE 1 F1:**
[figure not shown]
The schematic diagram of the trial design.

### Ethics and Dissemination

Our research group will protect the rights and safety of participants by full compliance with the Declaration of Helsinki and Good Clinical Practice (GCP) guidelines. Ethical approval of this trial has been granted by the ethics committee of the Beijing Children’s Hospital (ID: 2020-13-1). Written informed consent will be obtained from the parents of the participants. Adequate measures will be taken to ensure confidentiality of data collected in this trial. Results of this trial will be disseminated to the public through relevant academic and professional journals, academic conferences and workshops.

### Diagnostic Criteria of Early-Onset Neonatal Sepsis

The diagnostic criteria of EONS will refer to expert Consensus on the Diagnosis and Management of Neonatal sepsis (version 2019) (The Subspecialty Group of Neonatology, 2019).1) The suspected diagnosis of postnatal age in days (PNA) ≤3 contains any of the following: abnormal clinical manifestations, the mother has chorioamnionitis and premature rupture of membranes (PROM) ≥18 h. Sepsis can be ruled out if there are no abnormal clinical manifestations, including negative blood culture, and less than two consecutive non-specific blood tests (white blood cell count, immature neutrophil count, platelet count, C-reactive protein (CRP) and procalcitonin (PCT), etc.) at 24 h intervals.2) The patient has been clinically diagnosed with clinical abnormalities (Table 2) and met any of the following conditions at the same time: the blood non-specific tests ≥2 positive, the cerebrospinal fluid (CSF) test suppurative meningitis change, the pathogenic DNA detected in the blood.3) When the patient has clinical manifestations (Table 2), blood culture or CSF (or other sterile cavity fluid) culture positive, and the diagnosis confirmed.

**TABLE 2 T2:** Clinical manifestations of neonatal sepsis.

System	Clinical manifestations
Whole body	Fever, hypothermia, poor response, poor feeding, edema, low apgar score
Digestive system	Jaundice, abdominal distension, vomiting or gastric retention, diarrhea and hepatosplenomegaly
Respiratory system	Dyspnea, apnea, cyanosisetc.
Circulatory system	Pale face, cold limbs, bradycardia, tachycardia, marbled skin, hypotension or capillary filling time >3 s
Urinary system	Oliguria and renal failure
Blood system	Bleeding and purpura

### Inclusion Criteria

Patients will be recruited for this study if they meet all of the following criteria:1) PNA ≤ 3;2) Term infants and preterm infants with gestational age (GA) ≥ 32 weeks;3) The EONS diagnostic criteria;4) Suitable for latamoxef treatment;5) Written informed consent signed by the parent or legal guardian of the neonates.

### Exclusion Criteria

Patients with any of the following exclusion criteria shall not be admitted to this study:1) Expected survival time shorter than the duration of the treatment cycle;2) Severe congenital malformations;3) Having the high risk of serious bleeding, such as disseminated intravascalar coagulation (DIC) and Vitamin K deficiency bleeding (VKDB) (Rajagopal et al., 2017; Araki and Shirahata, 2020):A. Decreased platelet count (≤150 × 10^9^/L);B. Significantly prolonged prothrombin time (PT, especially PT is more than twice over upper limit of the normal range);C. Prolonged activated partial thromboplastin time (APTT, is more than the upper limit of the normal range);D. INR ≥4 or a value >4 times the normal values in the presence of normal platelet count and fibrinogen level;4) Undergoing surgery within the first week of birth;5) Receiving other trial drug treatment;6) Having other factors that researchers believe are not suitable for inclusion.

### Recruitment Strategies

Inpatient neonates will be enrolled from Beijing Friendship Hospital, Beijing Obstetrics and Gynecology Hospital, and Children’s Hospital, Capital Institute of Pediatrics (Table 1). We’ll use advertisements for recruitment on social media, such as WeChat, QQ, etc. Associate chief physicians in the neonatal units of these three hospitals will be in charge of EONS patient recruitment.

### Randomization and Blinding

To minimize selective bias, Beijing Six Yuan Space Information Technology Co., Ltd (Six Yuan) has been entrusted to conduct a stratified blocked randomization by using a computer random number generator in the system of Six Yuan. Participants will be randomly divided into the conventional treatment group and the model treatment group with a ratio of 1:1. The randomized code of the trial, derived from the random system of Six Yuan, will be the unique identification code of participants. After assignment of the randomization code, researchers are un-blinded to the treatment regimen of latamoxef. Considering that the drug concentration detection and data analysis will significantly affect the conclusion of this trial, all the research assistants in charge of drug concentration detection and statisticians will be blinded to treatment assignment until the trial is completed.

### Intervention

After inclusion in the study, participants will be randomized into a conventional treatment group and a model treatment group. They will receive the following interventions at least 3 days. Conventional treatment group: latamoxef, 30 mg/kg q12h; model treatment group: latamoxef, 20 mg/kg, q8h. As steady-state plasma concentration of latamoxef will be reached after 18 h of dosing, the opportunistic blood sampling method will be used to collect samples for testing plasma drug concentration at initial stage of the treatment (18–72 h) (Table 3).

**TABLE 3 T3:** Study schedule of latamoxef RCT in EONS treatment.

Items	Study phases (The beginning of latamoxef treatment is set as 0 h)		
	Baseline (−3–−1 day)	Initial stage of treatment (18–72 h)	Before the end of latamoxef treatment
Informed consent form (ICF)	X		
Demographic information	X		
Medical history	X		
Diagnosis and determination of the treatment regimen	X		
Inclusion/exclusion criteria	X		
Get the random number	X		
Comorbid drug use	X	X	X
Weight	X	X	X
Vital signs^a^ and physical examination	X	X	X
Blood routine^b^	X	X	X
Blood culture	X	X	X
CRP and PCT	X	X	X
Liver and kidney function^c^ ^d^	X	X	X
Cerebrospinal fluid (CSF) examination (optional)^e^	X	X	X
Dose, frequency and time point of latamoxef administration		X	X
Detection of plasma latamoxef concentration		Random sampling point	
Sampling time of plasma samples		X	
Efficacy assessment			X
Adverse event assessment		X	X
Case report form (CRF)	X	X	X

a Vital signs include the temperature, blood pressure and oxygen saturation (SaO_2_).

b Blood routine tests include red blood cells, hemoglobin, white blood cells, and platelets.

c Liver function tests include alanine and aspartate aminotransferases, alkaline phosphatase level, total bilirubin, and gamma-glutamyl transferase.

d Kidney function tests include creatinine and blood urea nitrogen.

e CSF examination include CSF routine (characters, cells and Pandy’s test) and culture. This examination can be used when neonatologists suspect a patient has a neurological infection.

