### Outcome Measures

#### Primary Outcome

The primary outcome will be 70% fT > MIC, which is the target rate of 70% of patients having a free antimicrobial drug concentration exceeding the MIC during 70% of the dosing interval. 70% fT > MIC is appropriate to evaluate therapeutic efficacy of time dependent antibiotics in neonates (Craig, 1995; Wu et al., 2020). Based on PPK model of latamoxef, 70% fT > MIC will be calculated after testing plasma drug concentration at the initial stage of treatment (Table 3).

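### The concentration sample has no set time after dose, so calling the primary outcome for an infant sampled early in the interval leans on the prior PPK model

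*Protocol article*

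**What the plan says.** The Intervention section gives the regimens as "Conventional treatment group: latamoxef, 30 mg/kg q12h; model treatment group: latamoxef, 20 mg/kg, q8h". It then states that "the opportunistic blood sampling method will be used to collect samples for testing plasma drug concentration" during the 18–72 h stage. The matching cell of Table 3 reads "Random sampling point". Neither place restricts where in the dosing interval the draw falls, and neither gives a number of samples per infant.

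The Primary Outcome section defines attainment as "having a free antimicrobial drug concentration exceeding the MIC during 70% of the dosing interval". It also says how attainment is obtained: "Based on PPK model of latamoxef, 70% fT > MIC will be calculated after testing plasma drug concentration at the initial stage of treatment". Both times that such a calculation needs are collected in Table 3, in the rows "Dose, frequency and time point of latamoxef administration" and "Sampling time of plasma samples".

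**The concern.** Whether an infant attains the target depends on the free concentration at one point of the interval. A draw soon after a dose mainly reflects dose and volume of distribution and says little about elimination, which governs the level several hours later. When the sample is uninformative, the individual estimate moves towards the typical infant of the prior PPK model. That is the model behind the 60.2% and 80.1% in Sample Size Estimates, so the trial would then be a weaker independent test of the model's prediction.

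At stake are the accuracy of each infant's yes/no primary result and the attainment reported for each arm. The effect on the difference between arms is a separate question, taken up below.

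**Working it through.** **1. Deciding times.** For a concentration that falls through the interval, the free level exceeds the MIC for 70% of the interval exactly when it does so at 0.7τ. This gives 0.7 × 12 = 8.4 h (q12h) and 0.7 × 8 = 5.6 h (q8h).

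**2. Reproducing the protocol's attainment rates.** From the protocol: both regimens, MIC 2 mg/L, 60.2% and 80.1%. Assumed, because the article does not give them: one compartment, bolus dosing at steady state, unbound fraction fu = 0.5, V = 0.5 L/kg.

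Free level at time t = fu × (D/V) × e^(−kt) / (1 − e^(−kτ)).

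Setting it equal to 2 mg/L at 0.7τ:
- q12h: 30 × e^(−8.4k) / (1 − e^(−12k)) = 2, so k = 0.325 per h
- q8h: 20 × e^(−5.6k) / (1 − e^(−8k)) = 2, so k = 0.418 per h

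An infant attains the target if its k lies below the threshold for its arm. With log-normal k and normal quantiles 0.259 (60.2%) and 0.845 (80.1%), the log-SD of k is ln(0.418/0.325) / (0.845 − 0.259) = 0.43. The median k is 0.325 × e^(−0.259 × 0.43) = 0.291 per h, so median clearance is 0.291 × 0.5 = 0.145 L/h/kg. With V also varying (CV 25%), a clearance log-SD of 0.40 gives both rates.

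The typical k of 0.291 is below both thresholds, so the typical infant attains in both arms. Shrinkage towards that infant therefore pushes estimated attainment upwards in both arms.

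**3. Classification.** Each simulated infant receives a MAP (empirical Bayes) estimate from its sample and the known dose and sampling times, and is classified from that estimate. The model step is thus included in every figure below. The ranges cover fu 0.4–0.6, CV of V 20–40% and residual error 15–35%, with a correct model without covariates.

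| Samples per infant | Misclassified, q12h | Misclassified, q8h |
|---|---|---|
| One, uniform over the interval | 9–15% | 7–11% |
| One, first 30% of the interval | 18–28% | 12–18% |
| One, last 40% of the interval | 3–9% | 3–8% |
| Two, uniform over the interval | 5–9% | 4–7% |

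For scale, with the protocol's 57 infants per arm, 9–15% is 57 × 0.09 = 5 to 57 × 0.15 = 9 infants in the q12h arm. Late samples (3–9%) give 2 to 5.

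At the base values (25% CV of V, 25% residual error), one any-time sample misclassifies about 12–14% (q12h) and 9–10% (q8h). A second-half sample misclassifies about 6% and 5%.

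**4. Attainment by arm.** If true clearance is 30% above the model, one any-time sample overstates attainment by about 5–9 points per arm, a first-half sample by about 9–15, and a second-half sample by about 1 or less. If clearance is 25% below the model, any-time sampling shifts attainment by at most about 2 points (for example 0.82 true, 0.803 estimated).

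**5. Difference between arms.** With uniform timing and a correct model, true against estimated was 0.201 against 0.200 (15% error), 0.209 against 0.217 (35% error), and at worst 0.183 against 0.220. With clearance 30% higher, one run gave 0.230 against 0.266. Early draws alone can do more (about 0.19 becoming 0.24). Late samples gave 0.202 against 0.204, and 0.252 against 0.256 with the higher clearance.

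**The case against.** The best defence is that infants are not classified from a raw level. The PPK model takes the recorded dose and sampling times, so a sample away from 8.4 h or 5.6 h can still be used, and opportunistic sampling with a population model is a deliberate choice. This stands against any claim that an early sample in itself produces a wrong result. It does not remove the point, because the figures above already include that step. Recording the time of an early sample does not give it information about late concentrations.

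Second, the size depends on assumptions. One sample per infant is the unfavourable reading, since the text speaks of samples in the plural, and two any-time samples remove much of the error. The Introduction names current weight, birth weight and postnatal age as covariates of clearance, and using them would sharpen the prior. Both stand.

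Third, sampling detail may sit in the implementation protocol mentioned under Quality Control. That could settle the number of samples. But the article does state a timing rule, and the rule is unrestricted.

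A reader might infer more than the documents support:
- *That many infants will be misclassified.* The documents give no error rate, and the simulated ones are conditional.
- *That the treatment comparison is invalid.* Errors in the two arms largely offset one another. The gain from late samples lies mainly in individual results and attainment by arm.
- *That the q12h arm is always less accurate.* With clearance 30% higher, one run gave 16% in both arms. Specificity with uniform timing was often lower in the q8h arm (0.62–0.82 against 0.78–0.88).
- *That the text and Table 3 contradict each other.* In a schedule cell, a random point most naturally means an unscheduled one, which is what opportunistic sampling provides.
- *That draws do cluster early, or at different phases by arm.* Nothing in the article says so.

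**Conclusion.** The point holds in a limited form. The stated rule leaves time after dose open, although that time determines how much a sample tells about the sole primary outcome. The less it tells, the more the result depends on the prior model.

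With one sample per infant, misclassification is roughly 7–15% under uniform timing and 12–28% if draws cluster early, against 3–9% with late-interval samples. Attainment in each arm is overstated by several points if clearance exceeds the model. The arm difference is distorted only modestly, by about 0–4 points with uniform timing. All of these figures rest on assumed volume, unbound fraction, between-infant variation and residual error, and on a prior without covariates. The deciding times of 8.4 h and 5.6 h need only that the level falls through the interval.

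The change is worth making because it is small and protects individual classification and the reported attainment rates. It is not needed to rescue the comparison between arms.

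**What to change.** In the Intervention text and Table 3:
- Replace the random-point entry with an instruction that, where routine care allows, the PK sample is taken with a routine draw in the second half of the dosing interval (after 6 h for q12h, after 4 h for q8h). An earlier draw is accepted when no late one is available.
- State that all available samples, with their times, enter the PPK model. Early samples are kept, not discarded, and a second sample helps wherever one exists.

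In the analysis:
- Tabulate time after dose by arm.
- Add a sensitivity analysis of the primary outcome limited to infants with a late-interval sample.

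The cost is a line or two of text, plus a table and one analysis from data that Table 3 already collects. Sites must check the dose clock when timing routine draws. Some infants will still have only an early sample, and for them the instruction changes nothing.
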